### Criteria for discontinuation

Criteria for discontinuation of a participant

Participants who no longer wish to remain in the study will be discontinued.

#### Criteria for discontinuation of the study

An interim analysis by the statistical team is planned after 50 % of women have completed the study. These results will be reviewed by the Data Safety and Monitoring Committee (DSMC). All adverse events and severe adverse events will be provided to the DSMC on an expedited basis. If the Committee feels the data confirms significant harm or benefit attributed to one of the study arms and recommends discontinuation of the arm or the study, enrolment will be stopped accordingly.

### Follow-up procedures

Delivery details of screened, consenting women who are not enrolled/randomized (e.g. who deliver before enrolment by caesarean section or vaginal delivery) will be recorded on the relevant screening form.

Participating women and their neonates must be followed up until discharge from the maternity and neonatal units. Therefore, we do not anticipate any loss to follow-up. The case report forms are available upon request.

For quality control, in a subset of cases a mobile phone or camera-based video and sound recorder with recorded time display may be set up behind the woman prior to random allocation. The recorder will be positioned so that the mother’s identity is not seen. The researcher’s recorded voice must document the time at which the randomization envelope is opened, the posture of the woman, the use of fundal pressure, and the time of delivery of the baby. The times will be transcribed from the time sheet and/or the recording to the paper CRF.

Recordings will only be used for research purposes; to assess quality of recording of timing of events. These recordings will be kept securely with other trial documentation in the research office and be accessible only to research staff. At the end of the study all recordings will be destroyed.

### Data entry

The data will be entered in OpenClinica™, a web-based, fully GCP-compliant data management system. The data analyst at WHO Geneva will develop the data management system, provide hosting, data back-ups and maintenance of the system.

A validation system will be built into the data management system to ensure consistency, accuracy and completeness of the data collected (range checks, consistency checks and skips). Double data entry will be performed and queries will be resolved as much as possible before discharge of the woman from hospital. First and second data entry will be done as soon as the case report forms are completed.

It is unlikely that serious side-effects of the intervention will occur. Adverse events and serious adverse events, whether thought to be related to the trial intervention or not, will be recorded by the researchers on the adverse events CRFs which will be submitted to the DSMC and the relevant ethics committees.

### Data protection procedures

The following measures will be taken to ensure participant confidentiality:Trial data for each participant will be identified by a unique ID number, not the participant’s nameThe trial register of names and trial ID numbers will be kept separate from the CRFsTrial documents will be kept securely under lock and key in the research offices and will not be accessible, other than to the researchersData will be entered by trial ID number in the password-protected data management system to which only trial staff will have accessThe trial report will not contain the names of any participantsAfter completion of the trial, the trial’s documents will be kept secured for five years

### Statistical methods

The sample size has been calculated to be powered to detect a reduction in the primary outcome of mean time (minutes) from randomization to delivery of > =3 min. A reduction of > =3 min was used due to the findings of the study by Api et al (2009) [31], that reported a time from randomization to delivery of 23.1 min (SD 12.2 min) in the control group (*N* = 56), and 18.6 min (SD 9.5 min) in the fundal pressure group (*N* = 34). We assumed that upright posture alone would likely lie between these two (i.e. approximately 20.0 min). Using the Bonferroni rule to control for multiplicity, alpha is divided by the number of comparisons (0.05/3 ≈ 0.02). We assumed a power of 90 % and alpha of 95 %. The study therefore requires 347 women in each arm, i.e. 1,041 women for all three arms. To allow for 10 % non-compliance, we aim to recruit 382 in each arm. The final sample size for the whole study is 1,145 women.

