### Data analysis

Data will be generated from the on-line data management system and analysed in SPSS. The primary analysis will be based on all subjects with outcome data available. Any participants with protocol violations, including women who no longer wish to receive their allocated intervention but are prepared to have data collected, will be analysed in the group to which they were allocated (intention-to-treat). Data from subjects who withdraw their consent will be excluded from the analysis and considered as lost to follow-up.

Baseline characteristics will be compared between groups to confirm the effectiveness of the randomization process in creating similar groups. Numbers and baseline characteristics of women lost to follow-up will also be compared between study groups to detect any imbalances.

Most study outcomes are categorical variables. For these types of variables, the number of subjects, number of missing values and percentages will be reported. Categorical variables will be compared between study arms as risk ratios with 95 % confidence intervals.

For continuous variables, e.g. time to delivery, the number of subjects, and number of missing values, minimum, maximum, means and standard deviations will be reported. Appropriate transformation of non-normal or skewed measurement will be performed. Means will be compared using t-tests for two independent samples, and 95 % confidence intervals will be calculated. If transformations do not generate a distribution approaching normality, medians and interquartile range (IQR) will be reported. The primary outcome of the study is “mean time (minutes) from randomization to delivery”. The survival technique log-rank test will also be used to compare the survival rates of the three groups, pairwise. Results will be reported according to CONSORT guidelines [22].

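### The per-comparison significance level is misstated (0.05/3 is 0.0167, not 0.02, and an alpha of 95 per cent is impossible), and the SDs behind 347 per arm are not given

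*Protocol article*

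**What the plan says.** The Statistical methods section of the protocol article says the trial is "powered to detect a reduction in the primary outcome of mean time (minutes) from randomization to delivery of > =3 min". It takes its planning values from an earlier study of fundal pressure: "23.1 min (SD 12.2 min) in the control group" and "18.6 min (SD 9.5 min) in the fundal pressure group". It places upright posture alone between the two, at about 20.0 min, and gives no SD for it.

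On multiplicity it applies the Bonferroni rule: "alpha is divided by the number of comparisons (0.05/3 ≈ 0.02". The next sentence reads "We assumed a power of 90 % and alpha of 95" per cent. The result is 347 women per arm, 1,041 in all, raised to 382 per arm and 1,145 in total for 10% non-compliance. The section does not say which SD, or which combination, produced 347.

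The Data analysis section says of continuous variables, with time to delivery as its example: "Means will be compared using t-tests for two independent samples, and 95 % confidence intervals will be calculated". For categorical outcomes: "Categorical variables will be compared between study arms as risk ratios with 95 % confidence intervals". It adds a log-rank test to "compare the survival rates of the three groups, pairwise". It mentions neither the Bonferroni rule nor an adjusted level.

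**The concern.** A Bonferroni level cannot be rounded upward without exceeding the total it is meant to protect. An alpha of 95 per cent has no meaning as a significance level. If it is taken as a 95% confidence level, it can be read either as the overall 5% before division or as an unadjusted 5% per comparison, and the text does not say which. The only confidence level named in the analysis section is 95%, the counterpart of an unadjusted 5% test.

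The primary outcome therefore has no single, correctly stated threshold in this document. That could matter for the conclusion. With 347 per arm and SD 12.2 in both arms, the smallest significant difference is 1.82 min at 0.05, 2.15 min at 0.02 and 2.22 min at 0.0167. An observed difference of 2 min would be significant under the first and not under the other two. The trial is unblinded, and its Discussion says the result will lead to this form of fundal pressure being promoted or to fundal pressure being discouraged.

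**Working it through.** **Inputs.** From Statistical methods: difference δ = 3 min, power 90%, SDs 12.2 and 9.5, three comparisons, 347 per arm. Allocation is 1:1:1. Sidedness is not stated; two-sided is assumed.

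**Level.** 0.05/3 = 0.01667. At 0.02 each, three tests have a bound of 3 × 0.02 = 0.06.

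**Reproducing 347.** Normal approximation: n per arm = (z₁₋α/₂ + z₀.₉₀)² × (σ₁² + σ₂²)/δ², with z₀.₉₀ = 1.282.

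- Both quoted SDs: 12.2² + 9.5² = 148.84 + 90.25 = 239.09, and 239.09/9 = 26.57.
- SD 12.2 in both arms: 2 × 148.84 = 297.68, and 297.68/9 = 33.08.

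| Alpha | z₁₋α/₂ | (z sum)² | n, SDs 12.2/9.5 | n, SD 12.2 in both |
|---|---|---|---|---|
| 0.05 | 1.960 | 10.51 | not needed | **347.5** |
| 0.02 | 2.326 | 13.02 | **345.8** (348 by t) | 431 |
| 0.0167 | 2.394 | 13.51 | 358.9 | 446.8 |

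Two input sets reproduce the plan's figure: alpha 0.02 with both quoted SDs, and unadjusted alpha 0.05 with the control SD in both arms. The exact Bonferroni level gives 359 or 447, not 347.

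**Power at 347 per arm for 3 min.** Power = Φ(δ/SE − z₁₋α/₂), with SE = √((σ₁² + σ₂²)/347).

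- SDs 12.2/9.5: SE = √(239.09/347) = 0.830, and 3/0.830 = 3.614. At 0.02: Φ(3.614 − 2.326) = 90.1%. At 0.0167: Φ(3.614 − 2.394) = 88.9%.
- SD 12.2 in both: SE = √(297.68/347) = 0.926, and 3/0.926 = 3.239. At 0.05: 90.0%. At 0.02: 81.9%. At 0.0167: Φ(3.239 − 2.394) = 80.1%.

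**Which SD pair is plausible.** The 3 min target is close to the assumed upright versus routine difference (23.1 − 20.0 = 3.1 min). GAP versus routine is 23.1 − 18.6 = 4.5 min. The SD of 9.5 belongs to a group that received fundal pressure. Neither the upright-only nor the routine arm is allocated the study's fundal pressure, so 12.2 in both arms is possible for that comparison. If the SD under upright posture alone lies between 9.5 and 12.2 (an assumption, since none is given), power at 0.0167 lies between 88.9% and 80.1%.

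**Family-wise error when no arm differs.** For three equal arms with a common variance, the chance that at least one pairwise test rejects is P(Q₃ > √2 × z₁₋α/₂), where Q₃ is the studentized range of three means.

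| Level per comparison | √2 × z | Bonferroni bound | Actual |
|---|---|---|---|
| 0.0167 | 3.386 | 5% | about 4.4% |
| 0.02 | 3.290 | 6% | about 5.2% |
| 0.05 | 2.772 | 15% | about 12.2% |

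**The case against.** The strongest reply is that the document's own inputs work. It writes 0.02, 3 min and SDs of 12.2 and 9.5, and on these 347 per arm gives 90.1% power. A reader might infer that 90% power plainly fails, and the documents do not support that. Correcting 0.02 to 0.0167 costs about one point on the same SDs. The fall to 80.1% requires SD 12.2 in both arms, which the text neither states nor rules out. This part of the reply stands.

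A reader might also infer that family-wise error will be 12.2%. That does not follow either. The 95% intervals appear in a general sentence on continuous variables and may be only a reporting convention. No sentence makes exclusion of zero the decision rule, and a separate statistical analysis plan was to be finalised before recruitment. The 12.2% is conditional on the intervals being used as the test. Likewise, the alpha of 95 per cent is most likely a slip for a 95% confidence level rather than a deliberate competing significance level. These points stand too.

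It may also be said that recruiting 382 per arm restores the power: with all 382 analysed and no dilution, it is 91.9% at 0.0167 with both SDs and 84.2% with SD 12.2 in both. But that margin is set aside for non-compliance. Under the stated intention-to-treat analysis, non-compliers stay in and dilute the effect, so the same margin cannot also pay for the alpha correction.

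What the reply does not remove is that 0.05/3 is not 0.02, that the next sentence is impossible as written, and that the SDs behind the sample size are undisclosed while two different alphas lead to the same figure. These are matters the article states wrongly or leaves ambiguous where it does speak, so a separate analysis plan does not cure them.

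**Conclusion.** The point holds as an error in the stated level and an ambiguity in the sample size. It does not show that the trial is badly underpowered.

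- Rounding 0.0167 up to 0.02 takes the bound to 6% and the actual family-wise error to about 5.2%. The claimed 5% control is exceeded, but only slightly.
- The error becomes material, at about 12.2%, only if the unadjusted 95% intervals are used to judge the primary comparisons.
- At the correct level, power for 3 min with 347 per arm is 88.9% with SDs 12.2 and 9.5, and 80.1% if 12.2 holds in both arms. The lower figure is a real possibility for upright versus routine, not an established one.

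These results assume two-sided tests, equal arms and the normal approximation, with a common variance for the family-wise figures.

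**What to change.** 1. In Statistical methods, write the per-comparison level as 0.0167 (0.05/3) and delete the alpha of 95 per cent.
2. State which SDs entered the calculation for each comparison.
3. Restate the power at 347 per arm for 3 min as about 89% with SDs 12.2 and 9.5, falling to about 80% if the SD is 12.2 in both arms.
4. In Data analysis, say that the three primary pairwise comparisons are judged at 0.0167 and reported with 98.33% intervals (1 − 0.05/3). The 95% intervals can stay for the other outcomes.

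Bonferroni is a valid choice here and need not be replaced; only its level needs correcting. The change is to wording in the protocol and the analysis plan, with no change in enrolment. The cost is slightly wider intervals for the primary outcome and a slightly lower stated power.

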#### Arm 3: Routine practice (recumbent/supine posture only)

The current posture as practiced in the participating sites will be used.

In all intervention arms, the trained birth attendant encourages the women to bear down. All other delivery procedures, such as fetal heart monitoring and routine oxytocin after the birth, are performed according to the usual hospital routine and will not differ between the groups.

For Arm 3 (routine practice), if the woman remains undelivered 30 min after randomization, fundal pressure or changes in posture may be considered necessary by the birth attendant according to routine local practice. Additional procedures or treatments performed at the discretion of the attendant will then be recorded in the study form.

At any stage of the labour, routine procedures such as change in posture, oxytocin administration, forceps or vacuum delivery or caesarean section will be available as considered indicated by the responsible clinician. If forceps, vacuum delivery or caesarean section is required, GAP and/or upright only posture will be stopped.

Electronic fetal heart rate monitoring is not routinely used in the study institutions in uncomplicated pregnancies; therefore, this equipment is unlikely to interfere with the administration of the interventions in this study. Auscultation of the fetal heart rate will be performed after each contraction following randomization. If electronic monitoring is considered necessary by the birth attendant, the GAP procedure will not interfere with monitoring as the monitor is positioned on the anterior aspect of the uterus while pressure is applied to the fundal aspect.

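### The 10% non-compliance allowance is added as if non-compliers left the analysis, so 382 per arm gives about 84–86% power at 3 minutes, not the stated 90%

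*Protocol article*

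**What the plan says.** All references are to the protocol article.

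- **Statistical methods.** The trial is "powered to detect a reduction in the primary outcome of mean time (minutes) from randomization to delivery" of at least 3 minutes. The planning values come from an earlier trial of fundal pressure: "23.1 min (SD 12.2 min) in the control group" and "18.6 min (SD 9.5 min) in the fundal pressure group". Upright posture alone is placed at about 20.0 minutes, with no SD given. On multiplicity, "alpha is divided by the number of comparisons (0.05/3 ≈ 0.02"). The next sentence gives power as 90% and alpha as 95%. The result is 347 per arm (1,041 in total).
- **Statistical methods, the allowance.** For 10% "non-compliance, we aim to recruit 382 in each arm", or 1,145 women overall.
- **Data analysis.** Women with protocol violations, including those who decline their allocated intervention but allow data collection, "will be analysed in the group to which they were allocated (intention-to-treat"). Only women who withdraw consent are excluded.
- **Follow-up procedures.** Mothers and babies are followed to discharge. "Therefore, we do not anticipate any loss to follow-up".

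**The concern.** Adding 10% to the head count is the right kind of step for women whose data are missing: they leave, and others replace them. It is the wrong kind of step for women who stay in the analysis without receiving their allocated intervention. They still count in the denominator, but they pull the difference between arms towards zero. Required sample size varies with the inverse square of the difference, so the correction has to be larger.

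The paragraph also gives more than one alpha. It invokes the Bonferroni rule, rounds the result upwards, and then appears to state an unadjusted 95% confidence level. A reader cannot tell which value produced 347 or which will be used for the three pairwise tests.

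What is at stake is how a negative result is read. The Discussion (Expected outcomes of this study) says that fundal pressure can be discouraged if it is not found useful. A conclusion of that kind leans on the type II error, which the plan puts at 10%.

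**Working it through.** **Inputs.** From Statistical methods: difference δ = 3 min, SDs 12.2 (control) and 9.5 (fundal pressure), power 90%, and alpha 0.05/3 rounded to 0.02. From Data analysis: a t-test for two independent samples. Allocation is 1:1:1. Sidedness is not stated, so two-sided is assumed.

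**Step 1: reproduce 347.** Use n per arm = (z₁₋α/₂ + z₀.₉₀)² × (s₁² + s₂²) / δ², with 12.2² + 9.5² = 239.09 and 12.2² + 12.2² = 297.68.

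| Alpha | SDs | Calculation | n per arm |
|---|---|---|---|
| 0.02 | 12.2 / 9.5 | (2.326 + 1.282)² × 239.09 / 9 | 345.8 |
| 0.05 | 12.2 / 12.2 | (1.960 + 1.282)² × 297.68 / 9 | 347.5 |
| 0.0167 | 12.2 / 9.5 | (2.394 + 1.282)² × 239.09 / 9 | 358.9 |
| 0.0167 | 12.2 / 12.2 | (2.394 + 1.282)² × 297.68 / 9 | 446.8 |

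The first two routes both reproduce the plan's figure; at 347 per arm the t-test power is 0.900 and 0.899 respectively. Neither route at exactly 0.05/3 does.

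**Step 2: reproduce the allowance.** 347 × 1.10 = 381.7, rounded to 382; 1,041 × 1.10 = 1,145.1. This is plain head-count inflation. Even for true dropout the usual form is 347/0.90 = 385.6.

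**Step 3: apply the plan's own analysis rule.** Assume 10% net non-compliance in a pairwise contrast, all of it kept in the allocated arm, with no effect in those women. The expected difference is 3.0 × 0.90 = 2.7 min. The inflation factor is 1/0.9² = 1.235, and 347/0.81 = 428.4, so 429 per arm.

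**Step 4: power of 382 per arm at 2.7 min (two-sided t-test).** For SDs 12.2/9.5 the standard error is √(239.09/382) = 0.791, and 2.7/0.791 = 3.413.

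- Alpha 0.02: 3.413 − 2.326 = 1.087, giving about **86.0%**.
- Alpha 0.05/3: 3.413 − 2.394 = 1.019, giving about **84.4%**.
- On the other route that yields 347 (alpha 0.05, SD 12.2 in both arms), the figure is 86.3%. On its own inputs, neither route keeps 90%.

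With SDs 12.2/9.5, 382 per arm holds 90% only up to about 4.7% non-compliance at alpha 0.02, or about 2.9% at 0.05/3.

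**Step 5: what the alpha rounding costs alone.** Three tests at 0.02 bound the familywise error at 3 × 0.02 = 0.06. At exactly 0.05/3 with SDs 12.2/9.5 and full compliance, 347 per arm gives 88.7% and 382 gives 91.8%.

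**Step 6: upright versus routine, at 2.7 min, 382 per arm, alpha 0.05/3.** The upright SD has to be assumed.

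- SD 12.2 in both arms: standard error √(297.68/382) = 0.883, power about 75%.
- Upright SD interpolated as the article interpolates the mean: 12.2 − (3.1/4.5) × 2.7 ≈ 10.3; standard error 0.817, power about 82%.

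**The case against.** **Part of the 10% may be consent withdrawal.** Data analysis excludes women who withdraw consent, and for them a head-count allowance is the right kind. This stands as a limit on the size. It does not rescue the statement: the paragraph says non-compliance, and Follow-up procedures expects no loss. Partial benefit in non-compliers would also shrink the gap.

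**The planning difference for GAP versus routine is 4.5 minutes.** Diluted by 10% to 4.05, power at 382 per arm and 0.05/3 is 99.7%. This is true and reassuring for that pair, but the claim the article makes is 90% power at 3 minutes.

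**The third pair is not short.** For GAP versus upright at 2.7 minutes and 0.05/3, power is about 91% with SDs 10.3/9.5 and about 94% with 9.5 in both arms. This stands, again with an assumed upright SD, so the shortfall is not uniform across comparisons.

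**Stronger readings that the document does not support.**

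- A reader might infer that no multiplicity correction entered the sample size, because 347 also reproduces at 0.05 with SD 12.2. The conflicting alpha statement leaves this possible, but the article openly shows the Bonferroni division, and 0.02 with the two quoted SDs fits equally well.
- A reader might infer that upright versus routine has only 75% power. That needs an SD of 12.2 for upright posture, which the article never gives.
- A reader might take the routine-arm rule as proof that non-compliance will exceed 10%: "if the woman remains undelivered 30 min after randomization, fundal pressure or changes in posture may be considered necessary by the birth attendant". With mean 23.1 and SD 12.2, roughly 22–29% would be undelivered at 30 minutes, depending on the distribution assumed. But the rule describes routine local practice, which is the comparator as defined. Those women may receive such measures, not will, and only their time after 30 minutes could be affected. It is not a non-compliance rate.

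**A protocol article may leave detail to the SAP.** That is so, but this is a published calculation at odds with the article's own analysis rule, not an omission.

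**Conclusion.** The power statement is wrong as written. The allowance treats non-compliers as absent, whereas the analysis keeps them. For GAP versus routine with SDs 12.2/9.5, the type II error at a 3-minute effect is about 14% (alpha 0.02) to 16% (0.05/3), against the stated 10%. This rests on two-sided tests, 10% net non-compliance in the contrast, all of those women remaining in the analysis, and no effect in them. It is therefore close to the upper end of the loss that a 10% rate can cause.

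The alpha wording is also defective: 0.02 does not hold the Bonferroni level, and the paragraph contradicts itself. If 0.02 and both SDs were used, the consequence is about one point of power, and with full compliance 382 per arm would still exceed 90% at 0.05/3.

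The matter is a should-fix. Neither the primary test nor the recruitment target has to change.

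**What to change.** Keep 1,145 women and rewrite the sample-size paragraph:

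1. State one two-sided alpha of 0.0167 for both the sample size and the three pairwise tests, and remove the statement of alpha as 95%.
2. State which SDs produced 347.
3. Restate power for 382 per arm at 3 minutes, with 10% non-compliance under intention-to-treat, as about 84% for SDs 12.2/9.5.
4. For upright versus routine, give a range with the SD marked as an assumption: about 75% at SD 12.2 in both arms, and about 82% if the upright SD is about 10.3.
5. Say whether the 10% includes women who withdraw consent.

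The cost is one paragraph and a less favourable power figure. No extra women, no change to care and no new analysis are needed. If 90% at 2.7 minutes were wanted instead, the number at alpha 0.0167 with SDs 12.2/9.5 would be 358.9/0.81 = 443.1, so 444 per arm (1,332 in total).
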